## Abstract

**Background:**

Prostate cancer (PCa) is the second most common cancer among men. New imaging-modalities have increased the diagnosed patients with limited number of metastasis after primary curative therapy, introducing so-called oligometastatic state. Stereotactic body radiotherapy (SBRT) is emerging as a low-toxicity treatment to erase PCa localizations and postpone androgen deprivation therapy (ADT). A deeper understanding of the predictive role of biomarkers is desirable for a targeted treatment selection and surveillance programs. The aims of the RADIOSA trial are:
Compare SBRT +/− ADT for oligorecurrent-castration-sensitive PCa (OCS-PCa) in terms of efficacy, toxicity and Quality of Life (QoL).Develop biology/imaging based prognostic tool that allows identifying OCS-PCa subclasses.

**Methods:**

This is a randomized phase II clinical trial, recruiting 160 OCS-PCa in 3 years, with progression-free survival (PFS) as primary endpoint. Three tasks will be developed:
Randomized clinical study (3 years for accrual and 2 years for follow-up and data analysis);Imaging study, including imaging registration and METastasis Reporting and Data System (MET-RADS) criteria;Pre-clinical study, development of a biobank of blood samples for the analysis of neutrophil-to-lymphocyte ratio and preparatory for a subsequent miRNA profiling.

We aim to determine which arm is justified for testing in a subsequent Phase III trial. A decision-tree algorithm, based on prognosis, biological phenotype and imaging profile, will be developed.

**Discussion:**

Recruiting will start in July 2019. SBRT will allow obtaining excellent PFS, local control, QoL and low toxicity. In SBRT arm, ADT deferral will allow for a drug-holiday, delaying the detrimental impact on QoL. A sufficient number of blood samples will be collected to perform biological patient profiling. A stratification tool will be established with an analysis of morphological and functional imaging, based on the use of MET-RADS criteria.

So, in conclusion, RADIOSA aims to define the optimal management of bone/nodal PCa relapses in a SBRT regimen. This study will increase our knowledge on low-burden metastatic PCa in the era of high precision and high technology personalized medicine, offering highly effective therapy in terms of clinical outcome and cost-effectiveness.

**Trial registration:**

The RADIOSA study was prospectively registered at clinicaltrials.gov (NCT03940235, May 2019).

## Background

PCa is the second most common cancer among men in the world (1.1 million new cases estimated) and death PCa related (estimated in over 300,000 deaths annually) correlates with metastatic state [1].

The advent of novel imaging techniques, such as Prostate-Specific Membrane Antigen Positron Emission Tomography (PSMA PET) and Whole-Body Magnetic Resonance Imaging (WB MRI), allows an increasing an early detection and diagnosis of metastases after primary curative treatment. In clinical practice the possibility to identify a few number of lesions is called “oligometastatic state” and it is considered an intermediate phase of tumor spread with limited metastatic capacity [2]. This state consists of low-volume disease, typically defined as the presence of up to 3–5 metastases [3] treatable with a local approach (such as surgery or radiotherapy) either with or without systemic therapy.

Patients with low-volume or oligometastatic disease have improved survival compared with those with high-volume metastases or a disseminated metastatic cancer [4]. While chemo-hormonal therapy is the standard of care for men with high-volume metastatic castration-sensitive PCa [5], in the low-volume metastatic PCa additional chemo-therapy did not demonstrate survival benefit [6], so SBRT is emerging as a promising low-toxicity treatment option for oligometastases both at diagnosis and recurrence [7]. Small-volume high-dose SBRT limited to metastatic site might potentially eliminate all macroscopic cancer foci prolonging the progression-free interval and postponing ADT. The aim of SBRT in this setting is to achieve local control and delay progression, and thereby postpone the need for further treatment.

Moreover, an open question in this framework is the patient QoL, to be evaluated in the balance of oligometastatic disease diagnosis, less treatment option and additional ADT-induced side effects. A deeper understanding of the predictive role of biomarkers is desirable for a targeted treatment selection and proper surveillance programs. The limitation associated with the use of the prostate-specific antigen (PSA) as diagnostic and follow-up marker stimulated significant investigations of several novel biological markers, such as blood-based parameters, microRNAs and cell-free DNA [8, 9]. However, this new approach requires a large amount of coherently collected data to give reliable and univocal results.

A further research frontier is the role of imaging in this setting of patients. Recently, the role of WB MRI has been proposed as a suitable solution for tumor detection and therapy evaluation in this setting of patients with performance at least comparable with the Choline positron emission tomography/computed tomography Ch-PET/CT [10].

Overall, clear-cut data and tools to guide a consensus about the optimal therapeutic choice for the individual clinical situation are not validated and the standard of care to recurrent PCa remains ADT, with significant side effect and deterioration of QoL [11].

## Methods/design

### Aim, design, and setting of the study

The present research project aims to define the optimal management of bone or nodal PCa recurrences in a SBRT regimen. As a final result, a decision-tree algorithm, based on prognosis, biological phenotype and imaging profile, will be obtained as a clinically useful tool.

This study will move forward our knowledge on low-burden metastatic PCa in the era of high-precision and high technology personalized medicine, offering highly effective therapy in terms of clinical outcome and cost effectiveness. The aim is to compare time to progression between the two study arms: SBRT only or SBRT and ADT. RADIOSA will be developed during the 5 years of the project and it is divided in two main phases.

### Study population

#### Participant characteristics

RADIOSA is a prospective monocentric randomized phase II study in which oligorecurrent PCa patients (1–3 lesions) are randomized to two treatments and the results with the longest time to progression is selected for further study [12].

#### Eligibility criteria

The inclusion criteria are as follows:
Histologically proven initial diagnosis of adenocarcinoma of the prostateBiochemical relapse of PCa following radical local prostate treatment (radical prostatectomy, primary radiotherapy or radical prostatectomy +/− prostate bed adjuvant/salvage radiotherapy) +/− ADT according to the European Association of Urology (EAU) guidelines 2016 [13] or after any salvage therapy if biochemical progression is diagnosed in the context of castration sensitive PCaNodal relapse in the pelvis, extra-regional nodal relapse (M1a), bone metastases (M1b) on Ch-PET/CT or WB MRI with a maximum of 3 lesionsSerum testosterone level > 50 ng/dl at the time of randomization (castration sensitive PCa)Eastern Cooperative Oncology Group (ECOG) performance status 0–1Age ≥ 18 yearsAbility to complete questionnaires about QoLWritten informed consent signed.

The exclusion criteria are as follows:
Presence of visceral metastasesMore than three metastasesInability to complete questionnaires about QoLPrevious invasive cancer (within 3 years before the prostate cancer diagnosis) apart from non-melanoma skin malignancies;Serious concomitant comorbidities or contraindication to SBRT and/or ADTMental diseases that cannot ensure valid informed consent

#### Methods of recruitment and random allocation

In phase 1 a hundred sixty consecutive patients will be enrolled at the Division of Radiation Oncology at the European Institute of Oncology (IEO), Milan, Italy within a multidisciplinary uro-oncology board.

There will be a 1:1 randomization between Arm 1 and Arm 2. Patients will be stratified according to PSA doubling time (≤3 vs. > 3 months) [14, 15], initial localization of metastases (node vs bone) and diagnostic imaging (PET vs. MRI) [Fig. 1].

**Fig. 1 Fig1:**
[figure not shown]
Study design

The patients will be randomized in either:
ARM 1: salvage SBRT for lymph nodes and/or bone metastases. All the radiologically documented lesions will be treated simultaneously.ARM 2: salvage SBRT (as described for ARM 1) + 6-month ADT (luteinizing hormone-releasing hormone (LHRH) agonist or antagonist). ADT should start within 1 week before the start of SBRT.

Phase 2 is complementary to Phase 1. After SBRT completion, patients will be followed-up with PSA and testosterone measurements every 3 months and with clinical examination at 3 and 6 months and every 6 months thereafter. Questionnaires for the assessment of QoL will be administered within 2 weeks prior to randomization, at 3 and 12 months, and yearly thereafter.

Blood and plasma samples for biological evaluation and randomization of patients, at 3 months from completion of treatment and at clinical relapse. The samples will be stored in the “European Institute of Oncology Biobank”.

Acute and late toxicity will be assessed according to the Common Toxicity Criteria for adverse events (CTCAE) toxicity criteria v4.3 [16], evaluated at 1 (acute toxicity) and at 3–6 months after the end SBRT and yearly afterwards (late toxicity). Time to castration-resistant disease will be assessed as time to start a systemic therapy (testosterone evaluation). A timeline of this study is summarized in Table 1.

**Table 1 Tab1:** Timeline of the study

	Screening	2 weeks within randomization	1 months after end of RT	3 months after end of RT	Every 3 months	12 months after end of RT	Every year	Biochimical relapse	Clinical relapse
Physical examination	x			x		x			
PSA/testosterone	x			x	x	x			
GS	x								
Previous treatments for PCa	x								
ECOG score	x								
Comorbidities	x								
Imaging	x								
Blood tests (NLR)		x							
Serum and plasma collection		x		x					x
Acute toxicity assessment			x						
Late toxicity assessment				x					
QoL		x		x		x	x		x
Cho-PET/TC or RM-WB								x	x

Moreover, a decision-tree algorithm, based on prognosis, imaging profile and biological phenotype will be developed: it will be addressed to identify recurrent PCa that remains oligometastatic and those that rapidly progress to a polymetastatic phase, thus allowing in the future to stratify patients who might avoid, or at least delay ADT, or not.

Data will be published at the end of the end of enrollment (2024).

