#### Discontinuation of the treatment/ disease progression

In case of biochemical progression (defined according to the EAU guidelines [13]) after SBRT, a new imaging scan should be considered: a WB MRI or Ch-PET/CT scan at time of biochemical progression or symptomatic progression and 6-montly afterwards until clinical progression will be performed. Further treatments (including ADT or other treatments according to the institutional policy) should not be started for biochemical progression without documented clinical progression on WB MRI or Ch-PET/CT. Repeated SBRT is allowed.

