## Discussion

Recently, the concept of ADT-free survival, intended as the time to the delayed start of ADT, in order to spare the related negative side effect, such as the increased occurrence of cardiovascular events and metabolic syndrome, that significantly affect the QoL [7]. The aim of SBRT in this setting is to achieve local control and delay progression, and thereby postpone the need for further treatments.

From the clinical standpoint, the emergence of castration resistance is usually a nearby antecedent of widespread disease progression, visceral involvement and death from PCa. Therefore, preservation of the responsiveness to ADT is crucial in the long-term management of patients with metastatic PCa.

Also, from socio-economic point of view, 12 months without ADT can be considered a consistent gain for the National Health System, especially considering the relevant costs of the new and spreading anti-androgens like Abiraterone and Enzalutamide [5].

Current knowledge is mainly based on retrospective and non-randomized studies, thus suffering from heterogeneous population (i.e., due to biased patient selection) and inappropriate sample power [18].

It is evident that also in the setting of metastatic PCa, prostatic definitive radiotherapy could find a place. First data derived from retrospective trials by Löppenberg et al. and Rusthoven et al. demonstrated an improvement in OS for patients who underwent radiation therapy targeting the prostate in comparison to those who received only hormonal treatment [19, 20].

The oligometastatic concept has been developed in the last years and recent trials show interesting results on adding local treatments (LCT) (such as radiotherapy or surgery) at standard therapy. Particularly, it is important to mention the results achieved by Gomez and Palma. Gomez et al., that conducted a randomized phase II trial on oligometastatic NSCLC, reporting a significant PFS benefit with LCT (both radiotherapy or surgery) vs maintenance systemic therapy (14.4 months vs 4.4 months respectively) [18]. In another randomized phase II trial, named SABR-COMET, a benefit in OS in the SBRT arm for the oligometastatic setting compared to palliative treatment was demonstrated (41 months vs 28 months) [21].

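### Time to castration-resistant disease is assessed by the start of a systemic therapy, which is not castration resistance and does not exclude ADT for castration-sensitive relapse or Arm 2's assigned ADT

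*Protocol article*

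**What the plan says.** Under Endpoints of the study, the protocol article lists time to castration-resistant disease as a secondary endpoint. ADT-free survival is a separate item in the same list. The only rule for measuring the former stands in the text below Fig. 1, in the section on recruitment and random allocation: "Time to castration-resistant disease will be assessed as time to start a systemic therapy (testosterone evaluation").

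Four other statements bear on that rule:

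- Eligibility criteria: serum testosterone must exceed 50 ng/dl at randomisation, and the article equates this with castration-sensitive disease.
- Arms, below Fig. 1: one arm is "ARM 1: salvage SBRT for lymph nodes and/or bone metastases", with no systemic therapy. The other is "ARM 2: salvage SBRT (as described for ARM 1) + 6-month ADT", given as an LHRH agonist or antagonist, and "ADT should start within 1 week before the start of SBRT".
- Discontinuation of the treatment/ disease progression: "Further treatments (including ADT or other treatments according to the institutional policy) should not be started for biochemical progression without documented clinical progression" on imaging. Once progression is documented on imaging, ADT may start, and castrate testosterone is not required. Repeat SBRT is also allowed.
- Follow-up, below Fig. 1: "patients will be followed-up with PSA and testosterone measurements every 3 months".

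**The concern.** Castration resistance means progression despite castrate testosterone, so it cannot come before castration. The rule instead dates the event by a treatment decision. A man with non-castrate testosterone who starts ADT for imaging relapse has castration-sensitive disease, yet nothing in the sentence stops him being counted as castration-resistant.

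The fault also differs by arm. One arm receives a systemic therapy by assignment and the other does not, so the result depends on a decision the rule leaves open: whether assigned ADT counts. Two analysts following the same sentence could report very different comparisons, and the choice could be made after the data are seen. The article's Discussion treats keeping disease responsive to ADT as crucial in long-term management, and this is the listed endpoint that addresses it most directly.

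**Working it through.** The plan gives no figure for this endpoint, so there is nothing to reproduce. The check applies the rule to each arm's assigned treatment and to the relapse provision.

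**Inputs**
- Total to be randomised: 160 (Calculation of the target sample size).
- Allocation: "There will be a 1:1 randomization between Arm 1 and Arm 2". Per arm: 160/2 = 80. Among the 152 before the loss-to-follow-up allowance: 152/2 = 76.
- Testosterone at randomisation: above 50 ng/dl in every patient.
- Systemic therapy by assignment: none in Arm 1; 6 months of ADT in Arm 2, starting in the week before SBRT.
- Systemic therapy after relapse: ADT or other treatment once clinical progression is documented, in either arm.

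**Three readings of the rule**

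| Reading | Arm 1 | Arm 2 | What is measured |
|---|---|---|---|
| A. Literal: any start of a systemic therapy counts and the bracket has no effect | Event at ADT or other systemic therapy after relapse | Event at assigned ADT, so about 80 of 80 around treatment start | Allocation; the comparison is fixed by design |
| B. Assigned ADT excluded; bracket adds no castrate requirement | Event at ADT or other systemic therapy after relapse | Same, after the assigned course | Largely ADT-free survival, already a separate endpoint |
| C. A start counts only if testosterone is castrate at that time | ADT started from non-castrate testosterone is not an event | Assigned ADT, started in men above 50 ng/dl at randomisation, is not an event | Nearer to the named endpoint, but still dated by a treatment decision |

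Reading B assumes that ADT-free survival runs to the start of ADT outside the assigned course; the article names that endpoint without giving a rule for it. The overlap is not complete, because a systemic therapy other than ADT would also count.

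**Does the bracket settle it?** The words about testosterone evaluation, with 3-monthly testosterone, suggest that some check of castrate status was intended. They give no level and no direction, and do not say whether progression must be present. A low value alone would not be enough: LHRH therapy is given to lower testosterone, so Arm 2 patients who are responding would also show castrate values during the assigned course.

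**Reading C still has a gap.** Repeat SBRT is permitted. A man who progresses at castrate testosterone and has SBRT again without a new systemic therapy would have no event, although he meets the ordinary meaning of castration resistance.

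None of the three readings, applied as written, gives time to castration resistance.

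**The case against.** The strongest defence is that this is loose wording, not a wrong rule. The bracket ties the assessment to testosterone. Listing the endpoint apart from ADT-free survival suggests that the authors did not equate starting ADT with resistance. The discontinuation section speaks of further treatments, which separates later therapy from assigned therapy. On that view reading C is the intended one and no Arm 2 patient has an event at treatment start.

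Much of this stands. A reader might infer that every Arm 2 patient has an event at baseline, or that any systemic therapy at all counts. The documents do not support either as a statement of what will be done. The sentence does not say any, it carries a testosterone qualifier, and the 80-of-80 result needs assigned treatment to be counted as an outcome. Even on that reading the timing is around treatment start, not at randomisation.

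Two further inferences should also be resisted:

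- The roughly 24 months in the sample size section is a cited estimate of delay to palliative ADT after metastasis-directed therapy. It is not a projection for this endpoint and does not show how early resistance would be recorded.
- The Discussion's phrase "the concept of ADT-free survival, intended as the time to the delayed start of ADT" describes a concept from the literature. It is not this trial's definition, and no fault in the ADT-free survival endpoint follows from it.

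The defence does not remove the core problem. Reaching reading C means supplying a castrate level, a progression criterion and an exclusion of assigned ADT, none of which the sentence contains. Nor is this a detail merely left to another document: the article does state a rule, and that rule names a different event from the endpoint.

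**Conclusion.** The point holds in a limited form. The stated rule does not measure castration resistance. It has no castrate-testosterone or progression criterion, and it excludes neither ADT for castration-sensitive relapse nor Arm 2's assigned ADT.

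Its size depends on the reading. In the literal case about 80 Arm 2 patients have the event around treatment start. If only assigned ADT is excluded, the endpoint largely duplicates ADT-free survival. If a castrate check is supplied, the main distortion goes, but the event is still dated by a treatment decision. The text does not settle which applies. The figure of 80 assumes full accrual of 160, equal allocation and that all of Arm 2 start their assigned ADT.

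Severity is moderate. This is one of several secondary endpoints in a phase II selection trial, and the primary endpoint, sample size and choice of arm do not rest on it.

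**What to change.** Replace the rule, for analysis purposes, with an explicit definition:

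- **Event:** documented PSA or imaging progression while testosterone is castrate, using the protocol's own 50 ng/dl cut-off.
- **PSA criterion:** write out the PSA-progression criterion that applies at castrate testosterone. Without it the definition is not yet operational, and the article does not supply one.
- **Time origin:** randomisation, in both arms.
- **Assessment:** the 3-monthly PSA and testosterone, plus imaging at progression, so that the event has the date of documented progression and not of a treatment start.
- **Assigned ADT:** state that starting the assigned 6-month course is not an event.

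Then reconcile the text below Fig. 1, the endpoint list and the discontinuation section, so that this endpoint and ADT-free survival are visibly different events. This concerns outcome definition only and asks for no change to treatment.

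The cost is endpoint wording; the PSA and testosterone schedule is unchanged. The downside is that fewer events will be seen within follow-up, so the comparison will be less precise.

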#### Treatment

Within 35 days prior to randomization, either a WB MRI or a Ch-PET/CT is mandatory to confirm a diagnosis of oligorecurrent disease, with a maximum of 3 pelvic/extra-pelvic lymph nodes and/or bone metastases, and to exclude visceral disease.

According to SBRT technique, high doses will be delivered to small volumes in few fractions (≤5). In our framework, a schedule of 30 Gy in 3 fractions every other day (equivalent dose EQD2 = 98.6 Gy, considering α/β = 1.5 Gy), or equivalent regimens depending on disease site location will be used. Treatment planning and delivery will be performed using dedicated systems, such as Iplannet-Vero (Brainlab-Mitsubishi) and Multiplan-CyberKnife (Accuray), Eclipse-Trilogy (Varian) and Tomotherapy (Accuray). As far as image-guidance is concerned, Vero, Trilogy and Tomotherapy use a pre-treatment cone-beam CT whereas CyberKnife is based on intrafraction X-Rays. Thus, CyberKnife needs fiducials or spine tracking. CyberKnife is preferred when particular attention to critical structures is required and spine tracking is possible. Strict quality assurance protocols will be implemented to ensure the accuracy in dose delivery.

#### Endpoints of the study

The primary objective is to compare the progression-free survival (PFS) defined as the absence of new metastatic lesions (local, regional or distant) between the two arms.

The secondary endpoints are as follows:
comparison of overall survival (OS)biochemical progression-free survival (BPFS)ADT-free survivallocal controltreatment-induced acute and late toxicitytime to castration-resistant diseaseQoL between the two armsdevelopment of a dedicated biobanking (collection of plasma and serum) for further biological investigation of predictive/diagnostic factors for personalized treatmentthe preliminary evaluation of prognostic biomarkersthe correlation between imaging-derived parameters and treatment outcome

The present research project will be developed for 60 months, during which specific milestones will be achieved and documented.

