#### Calculation of the target sample size

The main endpoint of this study is time to progression (local, biochemical and clinical progression) in oligometastatic PCA patients. We designed a randomized phase II selection study in which patients are randomized to two treatments and the results with the longest time to progression is selected for further study [12]. The aim is to compare time to progression between the two study arms: SBRT only or SBRT and hormonotherapy, with α = 0.10 and β = 0.20. It is estimated that the median delay to start palliative ADT after metastasis-directed therapy is approximately 24 months [17]. In order to detect a 12-month difference in the main endpoint from 12 to 24 months, a total of 152 patients will be needed, using a two-sided hypothesis based on the F distribution. Assuming a 5% rate of loss to follow-up, a total of 160 patients will be accrued over 36 months with 24 months of additional follow-up. We expect an accrual rate of 53 patients per year.

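### The primary endpoint has two conflicting definitions, one without PSA progression and one with it, and the trial is sized on the second

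*Protocol article*

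**What the plan says.** The Abstract (Methods) describes a randomised phase II trial "with progression-free survival (PFS) as primary endpoint". *Endpoints of the study* gives the primary objective as a comparison of "progression-free survival (PFS) defined as the absence of new metastatic lesions (local, regional or distant"). The same section lists "biochemical progression-free survival (BPFS") and local control among the secondary endpoints.

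*Calculation of the target sample size* states: "The main endpoint of this study is time to progression (local, biochemical and clinical progression) in oligometastatic PCA patients". The 12 versus 24 month medians and the 152 patients are attached to that endpoint. *Aim, design, and setting of the study* uses the same label: "The aim is to compare time to progression between the two study arms: SBRT only or SBRT and ADT". *Participant characteristics* also says that the arm with the longest time to progression goes forward.

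The arms differ in one respect. Arm 2 adds "6-month ADT (luteinizing hormone-releasing hormone (LHRH) agonist or antagonist") to the SBRT that both arms receive. In both arms "patients will be followed-up with PSA and testosterone measurements every 3 months". *Discontinuation of the treatment/ disease progression* calls for a scan at biochemical or symptomatic progression, and "6-montly afterwards until clinical progression will be performed". Table 1 lists follow-up imaging only at biochemical and clinical relapse.

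**The concern.** A time-to-event comparison needs one list of events. Here PSA progression is an event in one section and not in another. In this population the difference matters, because PSA is measured every 3 months while scans follow relapse. A version that counts PSA would normally yield more events, and earlier ones, than a version that counts lesions.

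The choice also does not bear equally on the two arms. Patients are castration-sensitive at entry, and only Arm 2 receives ADT. PSA suppressed by ADT can postpone a biochemical event whether or not metastatic spread is affected. Since the primary comparison decides which arm goes to phase III, an unsettled definition leaves that decision open to a choice made after the data are known.

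**Working it through.** **1. The definitions side by side**

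| Section | Label | Biochemical progression | Local progression |
|---|---|---|---|
| Abstract, Methods | PFS | not stated | not stated |
| Aim, design, and setting | time to progression | not stated | not stated |
| Participant characteristics | time to progression | not stated | not stated |
| Endpoints of the study | PFS | separate secondary endpoint | new lesions may be local; local control is secondary |
| Calculation of the target sample size | time to progression | primary event | primary event |

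PSA cannot be read into the endpoints section, because biochemical PFS stands there as a secondary endpoint. It cannot be read out of the sample-size section, which names it. A third endpoint enters through the planning figure: the 24 months is introduced as the median delay to palliative ADT after metastasis-directed therapy, which is neither version of progression.

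**2. The plan's own figures**

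- The step from 152 to 160 reproduces: 152 / 0.95 = 160.
- The 152 does not follow from the stated inputs. The F test on exponential medians of 12 and 24 months (two-sided α 0.10, power 0.80) needs 27 events per arm, 54 in total.
- With uniform accrual over 36 months plus 24 months of follow-up, P(event) = 1 − (e^(−24λ) − e^(−60λ)) / (36λ), λ = ln 2 / median. This gives 0.895 and 0.689, mean 0.792, and 54 / 0.792 ≈ 69 patients.
- That is a separate matter. The 152 is used below only as the planned number.

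**3. What ADT could do to a PSA-based event**

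From the article: 152 patients, 1:1, 36 + 24 months, two-sided α 0.10, and the two medians it mentions (12 and 24 months) as Arm 1 values. Assumed: exponential event times, the same underlying disease course in both arms, and a PSA suppression period s of 6 or 9 months in Arm 2. The article gives no s. Two models bracket the effect:

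- *Masking only:* T₂ = max(T, s). Events inside the window surface when it closes; later events are untouched.
- *Full shift:* T₂ = T + s. Every Arm 2 event is delayed by s, including those long after ADT has ended.

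The share of Arm 2 events that masking can move is 1 − 2^(−s/median):

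- median 12: 0.29 (s = 6) and 0.41 (s = 9)
- median 24: 0.16 (s = 6) and 0.23 (s = 9)

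Simulated rejection by the two-sided 10% log-rank test:

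| Arm 1 median | No effect | Masking, s = 6 | Masking, s = 9 | Full shift, s = 6 | Full shift, s = 9 |
|---|---|---|---|---|---|
| 12 months | about 10% | 15% | 29% | 70% | 92% |
| 24 months | about 10% | 10% | 12% | 37% | 62% |

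Repeat runs agree to within about 3 percentage points.

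**The case against.** The strongest reply is that the harm is easy to overstate. Four stronger readings are tempting, and the article does not support them.

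- *With PSA included, the endpoint merely reads out PSA suppression by ADT.* The sample-size version also counts local and clinical progression, ADT lasts 6 months, and ADT may truly delay disease.
- *The false-positive rate is 70-92%.* Those figures need every Arm 2 event to be delayed, even events well after ADT. A delay of that kind is arguably a treatment effect. Temporary masking gives 15-29% at a median of 12 months and almost no inflation at 24.
- *Death and regrowth of treated lesions are left out.* PFS conventionally counts death, and a condensed article may leave event rules to the full protocol. The word local in the endpoints section is ambiguous about regrowth; it does not clearly exclude it.
- *The PSA event lacks a post-treatment reference.* Biochemical progression is referred to the EAU guidelines, which are not shown, so no defect can be demonstrated. A nadir rule for biochemical PFS could itself mislead in Arm 2, where the nadir would be measured under ADT.

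The section on disease progression does not settle the conflict either. It governs scans and further treatment, and scanning on to clinical progression fits either definition.

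These limits stand, but they concern the size of the bias and side issues. They do not touch the contradiction over PSA, which a statistical analysis plan could resolve only by overriding one of the protocol's own statements.

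**Conclusion.** The primary endpoint is wrong as written. Two sections give different event sets, the labels PFS and time to progression alternate, and the planning median belongs to a third endpoint. This rests on the text alone and needs no assumption.

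That counting PSA can favour Arm 2 also holds, but its size is uncertain. It runs from negligible (masking, Arm 1 median 24 months) to very large (full shift, Arm 1 median 12 months), given the assumed 6 to 9 months of suppression and exponential event times.

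A reader might infer that a lesion-based endpoint removes the problem. It does not. Follow-up scans are triggered by biochemical, symptomatic or clinical relapse, so suppressed PSA can also delay the detection of lesions in Arm 2.

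**What to change.** - Use one primary definition, under one label, in the Abstract, *Aim, design, and setting of the study*, *Participant characteristics*, *Endpoints of the study* and *Calculation of the target sample size*. Preferably this is time from randomisation to lesion-based progression documented on imaging, or death. State whether progression of an SBRT-treated lesion counts.
- Keep biochemical progression only in the existing secondary endpoint, biochemical PFS.
- Restate the planning medians for the chosen endpoint, since the 24 months describes the delay to palliative ADT.
- State as a limitation that scans are triggered by biochemical or symptomatic progression, so detection in Arm 2 may be delayed.

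**Cost:** the definition is a change of wording and needs no new data. The downside is fewer primary events than with PSA included, so power should be rechecked once the medians are restated. Removing the detection bias, as opposed to declaring it, would need scans at comparable times in both arms. That means new data, which wording cannot supply.
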